## Methods

### Study Design

This is a 2-arm, randomized, open-label, waitlist-controlled trial in community-dwelling people aged ≥75 years. We will also conduct a process evaluation of this study. Randomization in the ratio of 1:1 is stratified by participant frailty status (frail or nonfrail; Multimedia Appendix 1). Participant frailty was determined using the FRAIL (Fatigue, Resistance, Ambulation, Illnesses, and Loss of Weight) scale based on five components: *fatigue*, *resistance* (inability to climb stairs), *ambulation* (inability to walk a certain distance), *illness*, and *loss of weight* [28,29]. The intervention group will commence the monitoring program for 12 months upon enrollment. The control group will be waitlisted for the first 6 months and then commence the monitoring program in the subsequent 6 months. The steps involved for enrollment, randomization, intervention, control, and exit from the program are outlined in the study flowchart (Figure 2), and descriptions of the screening program are provided in the following sections.

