### Sample Size

In computing the sample size required to assess the primary feasibility outcome, we will evaluate the proportion of participants reporting being satisfied or very satisfied that their heart rhythm was monitored in the past 6 months in the intervention group versus the control group. We arbitrarily set that 50% of the participants in the control group will be satisfied or very satisfied. With reference to the literature that reported a proportion of 67% [30] to 82% [31] of older people were satisfied or very satisfied with the use of technology-enabled monitoring at home, we postulate that there will be an absolute 30% increase in satisfaction in the intervention group compared with the control group. Our study will have 80% power, using a 5% level of significance, to detect an absolute difference of 30% in satisfaction between the 2 groups. A sample size of 100 participants aged ≥75 years is required to assess the primary feasibility outcome

To calculate the sample size required to evaluate the primary clinical outcome of AF detection rate, we set an AF detection rate of 10% in the intervention group and 1% in the control group, in accordance with a recent study [22]. At 80% power, a 2-sided test, and α .05, we estimate that a sample of 200 participants will be needed to detect a significant difference in AF detection between the intervention and control groups. Therefore, a total of 200 participants will be recruited for this trial to assess the primary clinical outcome.

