### Randomization

Participants will be randomized to the intervention or control group on a 1:1 basis stratified by baseline measure of frailty (ie, frail or not frail according to the FRAIL score) [28,29] and using permuted blocks of sizes 4 and 6. The statistician has generated a randomization list using the RandomiseR package in R software (R Foundation for Statistical Computing) [32]. The randomization list will be input into the REDCap (Research Electronic Data Capture) [33] database, which captures participant demographic and baseline data and survey findings (Multimedia Appendix 1). The statistician and principal investigators will be unaware of patient allocation until after the completion of the study.

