### Analysis

All analyses will be conducted according to the principle of intention-to-treat. Continuous variables will be presented as mean (SD) or median with IQR and categorical variables as frequency and percentage. The key outcomes, namely participant satisfaction in the AF screening program, usability of the screening program, and the incidence of new AF detected over 6 and 12 months, will be reported as frequency and percentages and will be compared between the intervention and control groups using the chi-square test. Comparisons between groups (intervention and control) for other outcomes will be assessed using the chi-square test or Fisher exact test for categorical variables and Student *t* test or Mann-Whitney test for continuous variables as appropriate. We will consider 2-tailed *P*<.05 as statistically significant. The agreement between the ECG device automatic algorithm and clinician interpretation will be evaluated using κ statistics. Subgroup analyses will be performed based on age, gender, and location. Subgroup analysis by frailty will be performed to examine the potential impact of frailty on the outcomes, feasibility, and acceptability of the program. The actual operational costs of delivering the project will be recorded and verified using invoices and receipts, including the costs of personnel involved in interpreting ECGs, which will be computed based on their hourly wages and the time they spent in their roles in this program. The resultant costs will be compared with the costs reported in the literature on the costs associated with the detection of AF in a similar older population. Missing data will be identified, and its causes will be described. Sensitivity analysis will be performed to examine the robustness of the findings [39].

Qualitative evaluation will be reported according to the COREQ (Consolidated Criteria for Reporting Qualitative Research) guidelines [40]. Interviews with patients and GPs will be thematically analyzed using an inductive approach [41]. Themes will be interpreted through the critical realism lens [37] and compared with the literature [42,43]. We will triangulate the quantitative and qualitative findings [44] from patient participants and GPs to acquire an in-depth understanding of the barriers to and enablers of implementing the screening program.

The process evaluation components [36], explanatory data, and anticipated outcomes are summarized in Table 2.

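### Randomisation is stratified by frailty but AF detection and satisfaction are tested with an unstratified chi-square: a valid test that can give up a little power if frailty is prognostic

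*Protocol article*

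**What the plan says.** In the Protocol article, Study Design states that 1:1 randomisation is "stratified by participant frailty status (frail or nonfrail", by the FRAIL scale. Randomization repeats this and adds the method, "using permuted blocks of sizes 4 and 6".

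Analysis then fixes the test. Satisfaction, usability and new AF are reported as frequencies and percentages and "will be compared between the intervention and control groups using the chi-square test". No stratified or frailty-adjusted comparison of the arms appears. Frailty enters the analysis once: "Subgroup analysis by frailty will be performed to examine the potential impact of frailty on the outcomes". One further sentence is general: "Sensitivity analysis will be performed to examine the robustness of the findings". It does not say that frailty will be adjusted for.

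For AF, Sample Size says: "we set an AF detection rate of 10% in the intervention group and 1% in the control group". It arrives at 200 participants for 80% power, two-sided α 0.05. For satisfaction it assumes 50% versus 80% and asks for 100.

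**The concern.** Stratified blocks hold the frail share almost equal in the two arms, so chance imbalance in frailty no longer adds to the variability of the between-arm difference. A pooled 2×2 chi-square still counts the frail versus non-frail difference as random variation. If frailty predicts the outcome, the test's variance is too large: it rejects slightly too rarely under the null and has slightly less power than the design allows.

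The protocol treats frailty as something that may matter. It is the stratification factor, its influence on the feasibility assessments is part of the second objective, and its impact on feasibility and outcomes is a listed outcome. The test is named in the text, so this is a choice already made and not a detail left to an analysis plan. At stake is a small amount of efficiency, mainly for AF, where the stated power has little to spare.

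**Working it through.** **Inputs from the article.** AF 10% versus 1%, satisfaction 80% versus 50%, 200 participants, two-sided α 0.05, 1:1 allocation within frailty stratum. **Assumed, because the article gives no figure:** frail share 10% to 50%; frail to non-frail risk ratio for AF 1 to 5; odds ratio for satisfaction (frail versus non-frail) 1 to 0.25.

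**1. The plan's own figure.** Per arm, n = [z₀.₉₇₅√(2p̄q̄) + z₀.₈₀√(p₁q₁ + p₂q₂)]² / (p₁ − p₂)², with p̄ = 0.055:

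- 1.960 × √0.10395 = 0.632
- 0.842 × √0.0999 = 0.266
- (0.632 + 0.266)² / 0.09² = 0.806 / 0.0081 = 99.5, so 100 per arm and 200 in total (power 80.2%)

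The stated 200 reproduces as an unstratified comparison. The planned power therefore does not rely on stratification.

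**2. Size of the variance overstatement.** With arms balanced in each stratum s (share w, risk p), p̄(1 − p̄) = Σw p(1 − p) + Σw(p − p̄)². The pooled test uses the left side, but only the first term on the right contributes to the variance. Example under the null: overall risk 5.5%, 30% frail, risk ratio 5. Non-frail risk = 0.055 / (0.7 + 0.3 × 5) = 0.025; frail risk = 0.125.

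- Between-stratum part: 0.3 × 0.07² + 0.7 × 0.03² = 0.0021
- Total: 0.055 × 0.945 = 0.0520
- Overstatement: 0.0021 / 0.0520 = 4.0%
- Effective cut-off: 1.96 / √0.96 = 2.00, so a nominal 5% becomes about 4.5%

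With a risk ratio of 1 the between-stratum part is zero and nothing is lost.

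**3. Simulation for AF**, 200 participants, near-equal allocation within strata, 200,000 trials per setting, no continuity correction. Ranges run over frail shares of 10%, 20%, 30% and 50%. The null is 5.5% in both arms.

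| Frail/non-frail risk ratio | Power, chi-square | Power, CMH | Type I, chi-square | Type I, CMH |
|---|---|---|---|---|
| 1 | 86.2-86.4% | 86.3-86.4% | 4.7-4.8% | 4.7-4.8% |
| 2 | 86.2-86.4% | 86.7-86.8% | 4.6-4.7% | 4.7-4.8% |
| 3 | 86.3-86.5% | 87.0-87.4% | 4.6-4.7% | 4.7-4.9% |
| 5 | 86.3-86.6% | 87.5-88.3% | 4.3-4.4% | 4.8-5.0% |

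The largest gain in this run is 1.9 points. A repeat with exact balance (100,000 trials per setting) gave 85.3-85.5% versus 85.4-85.6% at ratio 1 and 85.6-86.1% versus 86.7-88.7% at ratio 5. The largest gain there was 2.5 points, and the chi-square type I error at ratio 5 was 3.9-4.1%.

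**4. Simulation for satisfaction**, 20% or 50% frail.

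- 200 participants: both tests have at least 99.5% power in every setting.
- 100 participants: odds ratio 1, 89.6-89.7% (chi-square) versus 89.4-89.5% (CMH); odds ratio 0.25, 90.6-90.7% versus 91.4-92.0%.
- The largest loss from CMH, with frailty not prognostic, is 0.3 points at 80 participants.
- Under the null with odds ratio 1, both tests reject in about 5.5-5.8% of trials. This is a small-sample feature that they share and is unrelated to stratification.

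**5. Sparse AF cells.** Expected events: 100 × 0.10 + 100 × 0.01 = 11. With 20% frail and no frailty effect, the frail control cell expects 20 × 0.01 = 0.2 events. An exact stratified test is therefore natural, but its form matters. In the exact-balance run the fully exact stratified test had 76.8-79.0% power (type I error 2.1-2.4%), and its mid-P form had 84.1-85.9% (3.9-4.1%). The unstratified Fisher test has 76.9%. The ordinary CMH test stayed between 4.4% and 5.1%.

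**6. Point estimate.** With equal arms in each stratum the Mantel-Haenszel weight n₁n₀/n is proportional to stratum size, so the Mantel-Haenszel and crude risk differences are the same. Under blocks of 4 and 6 they nearly coincide.

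**The case against.** The case for leaving the plan alone is good on several counts. The chi-square controls type I error. The sample size is itself an unstratified calculation, so test and power calculation agree. A gain above about one point needs frailty to be a strong predictor of AF, and the article offers no evidence on that. Nor does it say that frailty was stratified to gain precision; stratifying also balances the arms for the planned frailty subgroup analysis. All of this stands, and it limits the point to a minor efficiency and consistency improvement.

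A reader might infer more than the documents support:

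- *That precision is always lost.* It is lost only if frailty is prognostic. With no frailty effect the tests are equal for AF, and CMH is marginally worse for satisfaction at 100 participants.
- *That satisfaction gains about three points.* With 30% frail and control satisfaction of 60% (non-frail) and 25% (frail), an odds ratio of 2.2 does give about 70% versus 73%. That effect is smaller than the planned 50% versus 80%. At an odds ratio of 5, which is close to the plan, power is 99.8% versus 99.9%.
- *That the crude estimate is mismatched to the randomisation.* Under balanced strata it hardly differs from the stratified one.
- *That every other between-arm comparison should be stratified too.* No benefit was shown for those.

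What the objection does not answer is that the change is almost free, and that a subgroup analysis by frailty is not a stratified test of the main comparison.

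**Conclusion.** The mismatch is real and fixed in the text; its consequence is small. The unstratified chi-square is valid. If frailty is strongly prognostic it becomes mildly conservative, with type I error about 4.1-4.4% (3.9% in the lowest setting run). It can then cost 0 to about 2 points of power for AF at 10% versus 1% with 200 participants, and essentially none for satisfaction at 50% versus 80% with 200. These sizes rest on assumed frail shares of 10-50% and assumed frailty effects. There is no bias, no type I inflation from stratification, and no shortfall against the planned 80%. Confidence is high in the mismatch and its direction, and low in where within the range the loss would fall.

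**What to change.** In Analysis, make the main between-arm comparison of AF detection and of satisfaction a Cochran-Mantel-Haenszel test stratified by the frailty stratum used at randomisation, without continuity correction. Report a Mantel-Haenszel risk difference with 95% CI, and keep the plain chi-square as supportive. The other comparisons can stay as they are.

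For AF, with about 11 events expected, use an exact version of the stratified test and state which form. The mid-P form is preferable, because the fully exact form would take power to about 77-79%, under the planned 80%. Mid-P costs about one point against the plain chi-square if frailty is not prognostic. If that is unwelcome, the ordinary CMH test held its level in the settings run.

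The cost is a sentence or two of wording. Frailty is already recorded before randomisation. The ordinary CMH test loses at most about 0.3 power points if frailty is not prognostic. The change should be made before allocation is revealed, so that there is no later choice between stratified and unstratified P values.

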**New atrial fibrillation detected**
Frequency of occurrence and proportions at 6 months—via electrocardiogram collected at the central monitor (during intervention) and self-report and confirmation with medical records or electrocardiogram (during waitlist control period)

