**Results:**

This study will establish the feasibility and effectiveness of implementing the intervention in this patient population. The primary clinical outcome is the AF detection rate, and the primary feasibility outcome is the patient satisfaction score. Other outcomes include appropriate use of anticoagulant therapy, participant recruitment rate, program engagement (eg, frequency of ECG transmission), agreement in ECG interpretation between the device automatic algorithm and clinicians, the proportion of participants who complete the trial and number of dropouts, and the impact of frailty on feasibility and outcomes. We will conduct a qualitative evaluation to examine the barriers to and acceptability and enablers of implementation. Ethics approval was obtained from the human research ethics committee at the University of Sydney (project number 2020/680). The results will be disseminated via conventional scientiﬁc forums, including peer-reviewed publications and presentations at national and international conferences.

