### Objective

Our study objectives are to (1) compare AF ascertainment rates in the intervention and control groups; (2) evaluate the feasibility of the intervention, including assessing participant satisfaction, acceptability, barriers, and enablers and how frailty influences these assessments; and (3) assess agreements between the ECG device automatic algorithm and clinician interpretation.

Alongside these objectives, the specific objectives of the process evaluations are as follows:

To assess the fidelity of the screening program (ie, whether the intervention was delivered as intended), participant engagement with the intervention in terms of the frequency of ECG recordings, and reach (eg, the socioeconomic and frailty profiles of participants and how these profiles affect the engagement and outcomes)To evaluate the feasibility of the screening program from the perspective of participants and clinicians to gain a deeper understanding of barriers and enablers; this includes an examination of the mechanisms of impact; that is, an examination of the potential causal mechanisms through which the intervention results in the adoption of self-screening by understanding how patients and clinicians interact with the screening programTo explore any factors external to the screening program that may have affected implementation (ie, the community-dwelling environment, access to health care services, and GP views and attitudes), including identification of resources and implementation processes required for effective uptake and implementation of the screening program

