### Control Group: Usual Care During Waiting Period

Participants allocated to the control group will have usual care and be told that they have been waitlisted to start the monitoring program in 6 months. During the 6-month waiting period, it is expected that participants in the waitlist group will visit their GPs as per their usual health care needs, and their GPs will provide care and referrals as usual.

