### Anticipated Challenges and Limitations

All study procedures have been designed to be conducted remotely by telephone or video interface to facilitate this study in the context of the COVID-19 pandemic. Therefore, the collection of baseline data and medical history relies on participants’ self-reported information. There is a potential for loss to follow-up in older patients who are frail; for example, participants do not record ECGs. We will attempt to minimize this by following up with patients when no ECG is received for 3 consecutive days. There may be a potential selection bias in this study based on the inclusion criteria. For example, this trial is limited to older people who can understand English and have a smartphone. These participants may come from higher socioeconomic communities and represent a more motivated cohort than the general population of older people.

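### AF diagnosed in usual care is captured unevenly between the arms in the 6-month primary clinical outcome

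*Protocol article*

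**What the plan says.** The Abstract states: "The primary clinical outcome is the AF detection rate". The first objective is to "compare AF ascertainment rates in the intervention and control groups". Textbox 1, under New atrial fibrillation detected, is the only place that names the data sources for this outcome. It takes the 6-month frequency and proportion "via electrocardiogram collected at the central monitor (during intervention) and self-report and confirmation with medical records or electrocardiogram (during waitlist control period".

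The text splits the sources by period. Controls wait unmonitored for the first 6 months (Study Design), so at month 6 the split by period is also a split by arm. By month 12 controls have been monitored for 6 months as well.

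During the wait, controls see their GPs as needed and "their GPs will provide care and referrals as usual". For monitored participants, the ECG Central Monitoring System section describes central review, with abnormal tracings referred to cardiologists. It describes asking the GP about treatment after the team has confirmed AF. On blinding, Study Design says: "This is a 2-arm, randomized, open-label, waitlist-controlled trial in community-dwelling people aged ≥75 years".

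**The concern.** A comparison of new AF between arms should count a diagnosis made in ordinary care in the same way whichever arm the person is in. As Textbox 1 reads, it does not:

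- **Intervention arm.** AF found by a GP or hospital and not seen on the device has no stated way into the count. Such cases are foreseeable. The article expects that some participants will not record (Introduction; Anticipated Challenges and Limitations), and participants are told to seek medical assessment for severe or worrying symptoms (Intervention Group). Leaving these cases out shrinks the recorded effect.
- **Control arm.** Ascertainment starts with the participant's own report. No record check is described for controls who report nothing, so a forgotten or misunderstood diagnosis is lost. That enlarges the recorded effect.

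The trial is open-label, so reporting may also respond to allocation. Masking of the analyst does not help with this: "The statistician and principal investigators will be unaware of patient allocation until after the completion of the study" concerns who knows the allocation, and the uneven capture arises earlier, when cases are collected.

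At stake are the size of the detection difference and its clean interpretation. Diagnoses that were never collected may be hard to recover afterwards.

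**Working it through.** **1. The plan's own figure.** Inputs from Sample Size and Randomization: 10% vs 1%, two-sided alpha .05, 80% power, 1:1. Pooled-variance formula, no continuity correction:

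n per arm = [1.960 × √(2 × 0.055 × 0.945) + 0.842 × √(0.10 × 0.90 + 0.01 × 0.99)]² / 0.09²

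= [0.632 + 0.266]² / 0.0081 ≈ 99.5, rounded up to 100.

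The total is 200, as stated, and power at 100 per arm is 80.2%. Uneven capture does not make this number wrong.

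**2. Expected events.** 100 × 10% = 10 in the intervention arm and 100 × 1% = 1 in the control arm. One case is one percentage point in either arm.

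**3. Shift in the recorded difference.** Let I be the intervention rate with every diagnosis counted, e the part of it found only outside the monitor, u the control rate with every diagnosis counted, and s the sensitivity of self-report.

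- Difference with full capture: I − u
- Difference as recorded: (I − e) − u × s
- Shift = recorded − full = u(1 − s) − e

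The documents give none of e, u (with full capture) or s. Assumed ranges: u = 1% to 3%, s = 0.5 to 1, e = 0 to 2%.

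| u | s | e | Shift (points) |
|---|---|---|---|
| 3% | 0.5 | 0 | +1.5 |
| 2% | 0.5 | 0 | +1.0 |
| 2% | 0.5 | 1% | 0 |
| any | 1 | 1% | −1.0 |
| any | 1 | 2% | −2.0 |

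The shift runs from −2.0 to +1.5 points against a planned 9. A plus sign means the recorded effect is too large.

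**4. What single cases do.** Uncorrected chi-square, 100 per arm:

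| Events | Difference | Ratio | P |
|---|---|---|---|
| 10 vs 1 | 9 points | 10 | .005 |
| 10 vs 2 | 8 points | 5 | .017 |
| 10 vs 3 | 7 points | 3.3 | .045 |
| 9 vs 3 | 6 points | 3 | .074 |

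Starting from the planned 10 vs 1, one or two further control cases leave the test below .05. Only when the control count is already 3 does one uncounted intervention case move it above. The effect is mainly on the estimate.

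**The case against.** The strongest reply is that finding more AF is what the intervention does. The objective is to compare ascertainment and the comparator is usual care, so most of the difference in route is the effect itself. That stands, and it confines the point to diagnoses made in usual care.

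The second reply is that Textbox 1 is a summary in a condensed article. It names sources without excluding others. Multimedia Appendix 1 contains a 6-month participant form that is not shown and may already ask both arms about new AF. This also stands: that a case counts only through the named route is an inference. It lowers confidence, but the stated rule still needs its wording corrected.

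Three stronger readings are tempting and are not supported:

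- **That intention-to-treat is broken.** The Analysis section says "All analyses will be conducted according to the principle of intention-to-treat". That governs analysis by allocated arm, and nothing removes non-recorders from their arm. A missed case is an ascertainment error.
- **That AF is checked to be new only in controls.** The confirmation in Textbox 1 establishes that the reported AF is present. Prior AF is an exclusion for everyone. The limitation that "the collection of baseline data and medical history relies on" participants' own accounts is declared and applies to both arms.
- **That uneven capture cuts power to 69%.** That is the exact chi-square power at 10% vs 2%, against 85% at 10% vs 1%. It describes a different true control rate. If self-report misses control cases, the recorded contrast grows and significance becomes more likely.

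**Conclusion.** The point holds in its narrow form. The only stated sources for the primary clinical outcome at 6 months capture usual-care AF differently by arm. On the assumed ranges the recorded difference could be off by about −2 to +1.5 points against a planned 9. The two errors pull in opposite directions, need not cancel, and their net sign cannot be known from the documents. The sample size is unaffected if 10% and 1% still hold, and the planned test is not overturned near the planned rates.

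This should be fixed, as a cheap improvement. Confidence is moderate, because the size rests on assumed inputs and the 6-month form is not shown.

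**What to change.** Amend the entry on new AF in Textbox 1 to one case definition for all 200 participants: AF first diagnosed between randomisation and month 6 by any route (central-monitor ECG, GP or hospital), confirmed by ECG or medical record. To support it:

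- ask the same new-AF question of both arms in the existing 6-month interviewer-administered questionnaire;
- apply the same GP or record check in both arms, whatever the participant reports;
- report programme-detected and usual-care-detected AF separately within each arm, so the contribution of the device stays visible.

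If the 6-month form already asks both arms about new AF, that part of the amendment is wording only. Otherwise the cost is one questionnaire item and one short GP query per participant. GPs are already told of enrolment (Recruitment) and invited to a survey (Data Collection). With 112 of 200 enrolled by December 2021 (Results), the change was still practicable. For anyone already past month 6, the GP query can be made retrospectively.

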### ECG Central Monitoring System

Qualified and trained study personnel, including a cardiac technician and clinical monitoring personnel with medical qualifications, will remotely review all ECGs and compare their diagnosis with the device’s automated diagnostic algorithm. If the ECGs are normal or have minimal abnormalities and the personnel are certain of their diagnosis, the ECGs will not be referred to a cardiologist. However, the personnel will refer all abnormal ECGs for diagnosis confirmation, or uncertain ECG abnormalities for clarification of diagnosis, to cardiologists or cardiac electrophysiology specialists. Participants’ ECGs will be classified into *low, moderate, high, and severe abnormalities* and managed as shown in Table 1. The research team will notify the participants and their GPs of AF or other clinically significant ECG abnormalities. A copy of an abnormal ECG will be forwarded to their GP. When an AF diagnosis is confirmed by the research team, the participant will be advised to see their GP. The participant will exit the screening program or opt to continue the monitoring program. The research team will contact the GP to obtain information about the treatment given to the patient.

**Table 1 table1:** Electrocardiogram (ECG) classification and management plan.

ECG findings	Classification	The study team will take the following actions
First-degree heart block	Low critical abnormality	If PR interval >300 milliseconds, notify and send ECG to GP^a^ within a week If PR interval is between 201 and 300 milliseconds, notify and send ECG to GP within the duration of participant’s enrollment in the study
Ectopic heartbeats (atrial ectopic and ventricular ectopic)	Low critical abnormality	As these are common and noncritical findings, notify GP at the end of the study
Atrial fibrillation, atrial flutter, nonsustained ventricular tachycardia, bradycardia <40 bpm^b^, second-degree heart block, nonsustained supraventricular tachycardia	Moderate critical abnormality	Notify and send ECG to GP within a week Advise patients to see their GP as soon as possible Contact patient to confirm review with their GP in the subsequent week

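### Textbox 1 names different sources for the primary clinical outcome (new AF) in each arm, and the article nowhere says that AF diagnosed in ordinary care is captured by the same rule in both.

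*Protocol article*

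**What the plan says.** The abstract states that "The primary clinical outcome is the AF detection rate", and the first objective is to "compare AF ascertainment rates in the intervention and control groups". Outcome Measurements lists new AF over 6 and 12 months without restricting the source. Textbox 1, under new AF detected, fixes the source for the 6-month comparison: "via electrocardiogram collected at the central monitor (during intervention) and self-report and confirmation with medical records or electrocardiogram (during waitlist control period".

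Four other places bear on the point:

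- **Intervention Group section.** Participants are told to go to their own doctor or a hospital if they have severe or worrying symptoms, so a diagnosis made off the monitor is foreseen.
- **Anticipated Challenges and Limitations.** "There is a potential for loss to follow-up in older patients who are frail; for example, participants do not record ECGs".
- **Analysis.** "All analyses will be conducted according to the principle of intention-to-treat", so people who stop recording stay in the denominator.
- **ECG Central Monitoring System.** "The research team will contact the GP to obtain information about the treatment given to the patient". This sentence follows the steps for AF that the research team has already confirmed, and it asks about treatment. It is not a search for AF found elsewhere.

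**The concern.** Both arms receive ordinary care for the 6 months, and the intervention arm has monitoring on top. A like-for-like comparison therefore needs AF diagnosed in ordinary care to be caught by the same rule in both arms. Read as written, the textbox does not do that.

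- **Intervention arm.** No route is given for counting AF first diagnosed by a GP or hospital. Examples are paroxysmal AF missed by a 30-second weekday trace, or AF in someone who never set up the device or stopped using it. This loss lowers the intervention rate and biases toward no difference.
- **Control arm.** The route starts with self-report, and records only confirm it. AF in the record of a control who does not know of it, does not mention it or cannot be interviewed is not found. This loss lowers the control rate and biases toward benefit.

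The point concerns AF first diagnosed after randomisation, not AF known before entry. Events are few, so a single case carries weight. Data never collected off the monitor cannot be recovered at analysis.

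**Working it through.** **1. The plan's own figure.** Sample Size: "we set an AF detection rate of 10% in the intervention group and 1% in the control group"; "At 80% power, a 2-sided test, and α .05, we estimate that a sample of 200 participants will be needed". With pooled variance, two-sided and no continuity correction:

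n per arm = [1.960·√(2·0.055·0.945) + 0.842·√(0.10·0.90 + 0.01·0.99)]² / 0.09² = (0.632 + 0.266)² / 0.0081 ≈ 99.5, so 100 per arm and 200 in total.

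The stated N is reproduced, with power 80.2%. About 10 intervention events and 1 control event are expected. One case more or fewer in an arm of 100 moves the difference by 1 percentage point.

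**2. Effect of one case on the planned chi-square test.** With 100 per arm, a and b events and m = a + b, the Pearson statistic reduces to 200(a − b)² / [m(200 − m)].

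| Intervention vs control events | Chi-square | P |
|---|---|---|
| 10 vs 1 | 200·81/(11·189) = 7.79 | .005 |
| 10 vs 2 | 200·64/(12·188) = 5.67 | .017 |
| 10 vs 3 | 200·49/(13·187) = 4.03 | .045 |
| 7 vs 1 | 200·36/(8·192) = 4.69 | .030 |
| 7 vs 2 | 200·25/(9·191) = 2.91 | .088 |
| 6 vs 1 | 200·25/(7·193) = 3.70 | .054 |
| 5 vs 0 | 200·25/(5·195) = 5.13 | .024 |
| 5 vs 1 | 200·16/(6·194) = 2.75 | .097 |

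At the planned counts the verdict survives one or even two extra control cases. At 5 to 7 intervention events, one case in either arm can reverse it: 5 vs 0 becomes 5 vs 1, 7 vs 1 becomes 7 vs 2, and 6 vs 1 becomes 7 vs 1. The Introduction cites monitored-arm yields of 3.8% and 5.3% in earlier screening trials, so counts in that region are plausible.

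**3. Each loss alone, at the planned rates.** The documents give no capture fractions, so these are assumptions. Power is by the formula in step 1.

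- Intervention arm, true total 10%, with 0.25, 0.5 or 1.0 percentage points diagnosed off the monitor and not counted: power falls from 80.2% to 78.8%, 77.3% or 74.1%.
- Control arm, true rate 1%, with 75% or 50% captured: the observed difference rises from 9.0 to 9.25 or 9.5 points (10 − 0.75 and 10 − 0.5).

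**4. Simulated trials.** 100 per arm, Pearson test, comparing the arm-specific rule with full any-source capture, at least 200,000 trials per row. The full-capture rate at 10% vs 1% is about 85% here, not 80.2%, because the test is evaluated on the binomial counts themselves and not by the normal approximation.

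| Monitor yield / usual-care rate | Assumed capture | Significant: arm-specific vs any-source | Verdict differs |
|---|---|---|---|
| 10% / 1% (planned) | 70% of control cases | 90.0% vs 85.5% | about 4.5% |
| 10% / 1% (planned) | 90% of control cases | 86.9% vs 85.4% | 1.6% |
| 10% / 2% | 70% of control cases | 79% vs 69% | about 10% |
| 8% / 2% | 50% of control cases | 70% vs 49% | about 21% |
| 8% / 2% | 70% of control cases, and 1% off-monitor AF uncounted in the intervention arm | 61% vs 60% | about 13% to 14% |

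In the third and fourth rows only control cases are lost, so the verdict can change in one direction only and the last column is the difference between the two rates. In the last row both losses act and nearly cancel on average, though individual trials still change verdict.

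**The case against.** The textbox is a one-line summary in a journal article. It names a source for each period and states no exclusion. A reader might infer that AF found off the monitor is expressly barred from the intervention count. The text does not say so: the restriction is inferred because no other source is named, and Outcome Measurements defines the outcome without reference to source. Multimedia Appendix 1, which holds the 6-month form, is not shown and may ask both arms about AF. A month-6 interviewer-administered questionnaire already covers satisfaction and anticoagulant use, so off-monitor AF could surface there. This lowers confidence. It does not remove the point, because asking about AF would not by itself make such a case count under the textbox rule.

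Some asymmetry is inherent. Controls have no monitor, and finding more AF because people are monitored is the effect under study, not a bias. A reader might extend the concern to the whole difference in detection; that would be wrong. It covers only AF diagnosed in ordinary care.

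A reader might also infer that one missed case can decide the trial as planned, or that the rule favours the programme. Neither is supported. At 10 versus 1 an extra control case leaves P=.017, and the two losses pull in opposite directions. The larger effects above need a usual-care rate or a yield other than the planned one, and capture fractions that have no source in the documents.

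**Conclusion.** The concern holds as a fault in a stated outcome rule, not as a missing detail. The article gives arm-specific sources for the primary clinical outcome, and no other section shown brings ordinary-care AF under a common rule. The sample size of 200 is unaffected.

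The size is modest at the planned rates: about 4.5% of trials change verdict if 70% of control cases are captured, and fewer with better capture. It grows as the yield falls toward the 3.8% to 5.3% of the cited trials, where 5 versus 0 and 5 versus 1 lie on opposite sides of .05. The net direction is unknown.

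Severity is should-fix, with moderate confidence. The conclusion rests on reading the textbox as the operative rule, on the unseen 6-month form not already settling the matter, and on assumed capture fractions.

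**What to change.** Replace the arm-specific wording in Textbox 1 with one rule for all 200 participants: new AF is AF first documented after randomisation and by month 6 from any confirmed source (programme ECG, GP or hospital ECG, or medical record).

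- Ask the same AF question in both arms at the month-6 interview that already takes place.
- Confirm positive reports in the same way in both arms.
- Report programme-detected AF separately, as the yield of the programme.

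This costs a change of wording, one interview question, and confirmation of the few positive reports. No extra participants are needed.

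Optionally, where consent allows, make the same GP-record check in both arms for participants who cannot be interviewed. This costs more: a short GP query for each such person, and possibly a consent or ethics amendment for those already enrolled (112 by December 2021, on verbal consent). It supports the common rule but is not a condition of it.
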